   3. *Pre-assessment.* Next, pre-assessment is completed by administering the Life Events Checklist (LEC; (Gray, Litz, Hsu, & Lombardo, 2004)), the PTSD Checklist for DSM-5 (PCL-5, Weathers et al, 2013) and items derived from the Service Receipt Inventory (SRI; (Chisholm, Knapp, et al., 2000)).
2. Randomization
   1. Randomization will be carried out by an independent trial unit (at University of New South Wales) Randomization will be performed using computerised software on a 1:1 basis.
3. PM+ Intervention
   1. *Appointments.* CHW who will make contact with participants for treatment to begin. The first PM+ session will be scheduled within a few days and no longer than one week after the baseline assessment. This therapist will plan five consecutive meetings with the participant.
   2. *Additional instrument.* At the start of PM+ and at the beginning of every session the Psychological Outcome Profiles instrument (PSYCHLOPS; (Ashworth, 2004)) will be administered. This instrument, in contrast to above named instruments will be administered by the therapist *to assess and monitor* progress on problems for which the person seeks help.
4. Post intervention assessment
   1. *1-week follow-up.* The post-intervention assessment (WHODAS, GHQ-12, PCL-5) will be scheduled 7 weeks after the pre-intervention assessment (i.e., 1 week after the 5^th^ PM+ session).
   2. *3-month follow up.*  The follow-up assessment - with the same questionnaires plus the life events measure (LEC) and SRI items but without the treatment satisfaction questionnaire - will be scheduled at 3 months after the 5^th^ PM session.

All instruments will be administered by trained research staff blind to the allocation status of the participants. All independent assessors will receive a five day training in administering the instruments, in general interview techniques, and in responding to participant distress, including, as mentioned, psychological first aid.

*Statistical power and sample size*

Since Study Phase 1 is a small exploratory RCT with 40 participants (20 participants per group), that does not aim to detect statistically significant differences in effectiveness, no power calculations have been (or should be) carried out.

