The CHWs, who will provide the PM+ intervention, already visit specific households as a standard part of their work with health facilities in the area. A local security assessment has indicated that it will be safe for screeners, assessors and CHWs to work at the household level.

All assessors and PM+ providers will receive pre-paid phone credit by the project to facilitate constant communications with each other and with the local World Vision office.

At the end of the study (at 4-5 months after inclusion), participants in the TAU condition will also be offered the PM+ intervention, if still indicated. If after the project, participants continue to experience psychological problems they will be offered additional support through aforementioned referral hospital, see above).

All adverse reactions and serious adverse events (SAEs) reported spontaneously by the subject or observed by the investigators or other staff members will be recorded by the research team. We consider an event a SAE if it is an undesirable experience occurring to a subject during the study, whether or not considered related to the research procedure. Although it is unlikely that SAEs would occur given the nature of the intervention, all adverse events and SAEs will be reported to the local independent advisory board.

The local advisory board will consist of: an independent medical officer (chair), an independent counselling psychologist with community mental health experience, the site principle investigator, and the clinical supervisor. All serious adverse events (SAE) and adverse events (AE) will be reported by the local principle investigators or supervisor to this advisory board. The chair or a nominated person from the advisory board will review SAEs within 48 hours.

Terms of reference of the advisory board are . 1. to establish rules and procedures governing its own meetings, consistent with the research protocols and standard; 2. to review SAEs within 48 hours, and all (S)AEs once a month and determine whether an (S)AE is likely to be related or unrelated to the intervention. 3 as necessary, recommend appropriate action in respect of ongoing trial conduct (such as referral to specialized care or installing extra assessment points for monitoring participants), and 4. follow-up to know whether recommended actions have taken place

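### The SAE definition contains no seriousness criterion, so every adverse event is an SAE, which contradicts the protocol's own two classes and two review tiers

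*Protocol*

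**What the plan says.** All the safety rules at issue stand in the protocol's Safety Considerations section.

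- **Definition.** "We consider an event a SAE if it is an undesirable experience occurring to a subject during the study, whether or not considered related". No separate definition of an AE follows.
- **Capture.** Adverse reactions and SAEs "reported spontaneously by the subject or observed by the investigators or other staff members will be recorded by the research team".
- **Reporting.** "All serious adverse events (SAE) and adverse events (AE) will be reported by the local principle investigators or supervisor to this advisory board". The same section also says that "all adverse events and SAEs will be reported to the local independent advisory board".
- **Review.** The board's terms of reference are "to review SAEs within 48 hours, and all (S)AEs once a month and determine whether an (S)AE is likely to be related or unrelated".
- **Expectation.** "Although it is unlikely that SAEs would occur given the nature of the intervention".

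On contact with participants, the Methodology section says of the PM+ arm: "This therapist will plan five consecutive meetings with the participant". Women in the enhanced treatment-as-usual (TAU) arm are referred to primary care clinicians, and the number of visits is not fixed. Assessors blind to allocation interview both arms after treatment and, in Phase 3, again at 3 months. Neither the assessment schedule nor the measures matrix contains an adverse-event question.

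**The concern.** An SAE rule has to separate the events that need fast review from the rest. This one separates events by whether they are undesirable and fall within the study period, which any AE would also satisfy. Staff then have two options. They can send every bad experience for 48-hour review, or they can apply a private threshold that may differ between people and between arms. Either way the number of SAEs reported at the end has no fixed meaning.

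The second matter is how events come to light. Both capture routes depend on someone speaking up or someone noticing, and the two arms do not have the same planned contact with study personnel. If harms are later compared between arms, part of any difference could reflect contact and not harm.

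**Working it through.** **Step 1: the definition against the rest of its section.** The protocol states no event rate or count, so there is no figure to reproduce. The check is a comparison of statements.

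| Statement in Safety Considerations | What it requires | Under the definition as written |
|---|---|---|
| AEs and SAEs are both named as reportable | Two distinguishable classes | One class: every AE meets the SAE definition |
| 48-hour review for SAEs, monthly review for all events | A subset that goes first | The subset is the whole set, so the faster tier covers everything |
| SAEs are unlikely | A rare kind of event | Any undesirable experience qualifies, in women whom the Ethics section describes as living with multiple stressors and traumatic events |
| Adverse reactions are recorded, adverse events are reported | One consistent term | The input and output of the process carry different names |

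No reading of the definition satisfies the first three rows together.

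**Step 2: extra contact in PM+.** Minutes from the session outlines:

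- Session 1: 30 + 20 + 20 + 15 + 5 = 90
- Session 2: 5 + 40 + 30 + 10 + 5 = 90
- Sessions 3 and 4: 5 + 25 + 25 + 20 + 10 + 5 = 90 each
- Session 5: 5 + 30 + 30 + 20 + 5 = 90

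Total: 5 × 90 = 450 minutes, or 7.5 hours.

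**Step 3: can the effect on recorded events be sized?** Take Phase 3 and equal true event rates. Let q be the chance that any one contact brings an event to light, and k the number of TAU nurse visits whose findings reach the research team. Both are assumptions, because the protocol gives neither. PM+ has 5 + 2 = 7 contacts after randomisation and TAU has 2 + k. The chance that an event is recorded after m contacts is 1 − (1 − q)^m, so the ratio of recorded events is [1 − (1 − q)^7] / [1 − (1 − q)^(2 + k)].

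| q | k = 0 | k = 2 | k = 5 |
|---|---|---|---|
| 0.05 | 3.09 | 1.63 | 1.00 |
| 0.10 | 2.75 | 1.52 | 1.00 |
| 0.30 | 1.80 | 1.21 | 1.00 |
| 0.60 | 1.19 | 1.02 | 1.00 |
| 0.90 | 1.01 | 1.00 | 1.00 |

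For q = 0.10 and k = 0, the ratio is 0.522 / 0.190 = 2.75. With 173 women per arm and an assumed true rate of 10%, that gives 173 × 0.10 × 0.522 = 9.0 recorded events in PM+ against 173 × 0.10 × 0.190 = 3.3 in TAU. The TAU figure would be 5.9 at k = 2 and 9.0 at k = 5. With more than five TAU visits the ratio would fall below 1. The illustration shows that an excess is possible; it does not give its size.

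**The case against.** Several points on the other side stand.

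- **A broad definition errs towards caution.** Read literally, every event is reviewed within 48 hours and no serious event escapes the rule. A reader might infer that self-harm or violence would go unattended, and the documents do not support that. Suicidality and severe disorder lead to hospital referral in either arm, and acute protection risks have their own response. What is lost is triage of reports and a meaningful count.
- **Capture is not by spontaneous report alone.** Staff observation counts too. The accurate word is passive.
- **An excess in PM+ is not established.** A reader might divide seven contacts by two and infer a 3.5-fold excess. That is only the limit as detection per contact approaches zero with no TAU visits at all. TAU women are referred to nurses trained in supportive counselling and psychological first aid, and attendance is monitored. Whether those nurses count as staff who report events is not stated.
- **No between-arm comparison of harms is stated** in Data Management and Statistical Analysis. The stated use of events is case-by-case review. A comparison may sit in a statistical analysis plan that is not at hand, so its absence is no fault here.
- **Some identical enquiry exists.** At 3 months both arms answer the Life Events Checklist, which covers events such as rape and serious injury, and service-use items that include hospital care. These overlap with adverse-event collection only in part, and the protocol does not link them to it.

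A reader might also infer that the advisory board cannot judge events fairly, because its four members include "the site principle investigator, and the clinical supervisor". Calling such a board independent is loose, but its membership is disclosed and its chair is an independent medical officer. Voting rights are a governance preference, and the absence of a data monitoring board is a reasoned choice in Quality Assurance.

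None of this answers the contradiction in the definition.

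**Conclusion.** The definition is wrong as written. It makes SAEs and AEs the same set, contradicts the classes, review tiers and expectation stated around it, and leaves any SAE count without a fixed meaning. This follows from the text alone and rests on no assumption.

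The ascertainment point is secondary and conditional. PM+ adds 7.5 hours of contact, capture is passive, and recorded events may therefore be higher in PM+. Under the assumed values (q from 0.05 to 0.90, up to five TAU visits, equal detection at every contact) the ratio lies between 1.00 and 3.09. The protocol gives no basis for choosing a value in that range. The contact counts apply to Phase 3 only, because the pilot has no 3-month assessment. The primary outcome, sample size and efficacy analysis are untouched.

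**What to change.** In Safety Considerations:

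1. Define an SAE by listed seriousness criteria, which the sponsor should choose (for example death, threat to life, hospital admission or lasting incapacity).
2. Define an AE separately, so that the 48-hour and monthly tiers apply to distinguishable sets.
3. Use one term throughout, reconciling the adverse reactions that are recorded with the adverse events that are reported.

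In the assessment schedule, have the blinded assessors ask one identical adverse-event question in both arms at the existing post-treatment assessment and, in Phase 3, at the 3-month assessment. Base any comparison of harms between arms on those answers. Spontaneous and observed reports should continue to go to the advisory board for individual review.

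The cost is a wording change and slightly longer interviews at visits that already take place. No additional visits, staff or participants are needed.

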On the informed consent form, patient information is included to inform participants that the field coordinator, or another clinician other than their therapist are available to them if they are upset by this study.

The principal investigator will inform the subjects and the WHO ERC if anything occurs, on the basis of which it appears that the disadvantages of participation may be significantly greater than was foreseen in the research proposal.

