**Quality Assurance**

Participants in the RCTs may directly benefit from their participation in the PM+ intervention, which is based on cognitive behavioural therapy (CBT) techniques (problem solving, stress management, behavioural activation, facing fears, and accessing social support) that are empirically supported and recommended by the WHO for use in low and middle income countries (Dua et al., 2011; Tol et al., 2013; WHO, 2010b). Their participation will furthermore inform local application of PM+ manual, and thus improve knowledge about delivering mental health interventions in the study area. Since PM+ is non-pharmacological and there is a broad evidence base for its use, it is unlikely that adverse effects due to the intervention will occur in Study Phases 1 and 3. Therefore, we believe that it is not necessary to install a Data Monitoring Safety Board for this study.

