**Ethics**

The project protocol will be reviewed by the Great Lakes University of Kenya, Nairobi and the WHO Ethics Review Committee.

No minors will be involved in this study. All participants will be adults older than 18 years.

Full information on the study will be provided in local, lay language before consent (written or oral as described above) will be obtained from each participant. This information will be read out to participants who are illiterate in the presence of a witness not affiliated with the study. We will be careful to ensure that potential participants clearly understand the implications of their involvement and that (a) they can withdraw their consent at any time without giving an explanation; (b) refusal or withdrawal of consent would have no impact upon any type of support they receive. The informed consent procedure is described in this protocol, and follows recommendations by WHO’s Ethical Review Committee (<http://www.who.int/rpc/research_ethics/Process_seeking_IF_printing.pdf>). This procedure includes: 1) oral and written information to consider participation; 2) a variant for illiterate participants, who may give consent through both a signature of a literate witness (not a member of the research team) and a thumb print.

People with recently developed, acute protection risks or recent trauma (i.e., in the past month) will be offered psychological first aid by the assessor (WHO, War Trauma Foundation and World Vision International, 2011) and linked to available support services/resources. Participants with recent trauma will also be offered psychological first aid by the assessor. All independent assessors will be trained in the Kiswahili version of the WHO, War Trauma Foundation and World Vision International (2011) guide on psychological first aid.

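### The safety board is called independent, but half its members are trial staff, and the text lets a staff member who reported an SAE do its 48-hour review and join the relatedness ruling

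*Protocol*

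**What the plan says.** All of the board's rules are in the protocol's Safety Considerations section.

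- **Label.** The section states that "all adverse events and SAEs will be reported to the local independent advisory board".
- **Membership.** The four members are "an independent medical officer (chair), an independent counselling psychologist with community mental health experience, the site principle investigator, and the clinical supervisor". The word independent is attached to the first two only.
- **Reporters.** AEs and SAEs "will be reported by the local principle investigators or supervisor to this advisory board".
- **Urgent review.** "The chair or a nominated person from the advisory board will review SAEs within 48 hours". No condition is placed on who the nominee may be.
- **Board tasks.** The terms of reference let the board set its own meeting rules. It is to review SAEs within 48 hours and all events monthly, decide whether each is likely to be related to the intervention, recommend action on trial conduct where needed, and check that the action was taken.

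Under Quality Assurance the protocol explains that PM+ is non-pharmacological and rests on established techniques, and concludes: "we believe that it is not necessary to install a Data Monitoring Safety Board for this study".

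**The concern.** The label and the membership list do not agree. A board that is half trial staff is not independent in the usual sense, and the protocol's own wording marks only two of the four as independent. The remaining two, "the site principle investigator, and the clinical supervisor", belong to the team whose trial is being judged, and the PI role is also among those that report events.

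What is at stake is the credibility of the harm assessment. Relatedness to PM+ is a judgement, and the people running the trial have an interest in how it comes out. This board is also the only safety board in the protocol, so any independence in that judgement has to come from here. The protocol itself foresees participants with suicidality or acute protection risks, so serious events are not a remote prospect even if harm from PM+ is thought unlikely.

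**Working it through.** The protocol gives no figure to reproduce on this point. The check is a count of roles and a reading of the rules side by side, all from Safety Considerations unless stated.

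**1. Composition.** Members listed: 4. Described as independent: the medical officer (chair) and the counselling psychologist, so 2. Trial staff: the site PI and the clinical supervisor, so 2. Trial-staff share = 2/4 = 50%. The independent members are not a majority.

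**2. Who may do the 48-hour review.** Eligible: the chair, or any nominated board member. Possible nominees other than the chair = 4 − 1 = 3. Of these, trial staff = 2 and independent = 1 (the psychologist). If the chair does not do the review, two of the three people who could stand in are trial staff.

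**3. Overlap of reporter and reviewer.** Reporters are the local PIs or a supervisor. The site PI on the board matches the first group in substance. The second match is less certain. The board has a clinical supervisor, while the reporting sentence says only supervisor, and the section on PM+ providers and protocol adherence describes one supervisor for each of three facility areas. That half of the overlap is the natural reading but is inferred. The point does not need it, because the PI overlap is enough.

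**4. Who decides relatedness.** The terms of reference give this to the board. No member is excluded, and there is no rule for an event that a member reported.

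**5. When an independent member is certain to be involved.** If the chair or the psychologist does the urgent review, that is within 48 hours. If a trial-staff nominee does it, the next review that the text guarantees is the monthly one. The independent look may therefore move from 48 hours to as late as the next monthly review.

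**6. Any other safety board.** None. Quality Assurance declines a data monitoring board.

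Steps 2 to 5 together show that the text allows one person to report an SAE, review it urgently and take part in the relatedness decision.

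**The case against.** The case for leaving the text alone has real substance.

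- **The chair comes first.** The first-named urgent reviewer is independent, and the psychologist may also be nominated. Self-review is the exception. This stands, and it limits the size of the problem.
- **The full board sees everything monthly.** Both independent members belong to it, so each event should reach them. This stands too.
- **Follow-up does not depend on the ruling.** The Follow-Up section requires every adverse event to be followed until specialist care is in place or the situation is stable.
- **The board sets its own procedures.** Recusal might be settled there. It might, but the protocol does not require it, and the board drafting those rules is half trial staff.
- **A data monitoring board was declined with reasons.** That choice is not disputed here. Its effect is that this board carries the whole independent check.

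A reader might also infer more than the documents support:

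- *That a nominee alone can rule an event unrelated, or close a harm signal unseen.* The nominee reviews, the board rules on relatedness, and the monthly review and follow-up duty still apply.
- *That relatedness is the only judgement of harm.* The same section has another, on whether the disadvantages of taking part exceed what was foreseen: "The principal investigator will inform the subjects and the WHO ERC if anything occurs". The board also recommends action on trial conduct.
- *That the site PI and clinical supervisor know the allocation.* The protocol states blinding for the assessors and does not say what these two know.
- *That a two-against-two vote could block a ruling.* No voting procedure is described.
- *That safety notices wrongly omit one ethics committee.* The Ethics section says that the protocol will be "reviewed by the Great Lakes University of Kenya, Nairobi and the WHO Ethics Review Committee". That concerns review of the protocol, not safety notices. The PI's duty to inform the WHO committee bars nobody else from notifying.

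**Conclusion.** The point holds as a contradiction between a label and a rule, with a practical gap behind it. The board is called independent while 2 of its 4 members are trial staff, 2 of the 3 possible stand-ins for the chair are trial staff, and no rule removes a member from an event that he or she reported. The consequence is possible self-review at the urgent stage, possible delay of independent sight of an SAE until the monthly review, and trial-staff participation in every relatedness ruling.

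This rests on two readings: that *a nominated person from the board* means any of its members, since no limit is given, and that the site PI is one of the local PIs who report. It does not rest on the supervisor overlap or on anyone's knowledge of allocation.

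No sample size, endpoint or efficacy analysis depends on it. It should be corrected because the change is nearly free and this is the only safety board, but it is not a flaw that undermines the trial.

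**What to change.** Amend the advisory board text in Safety Considerations in two places.

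1. After the 48-hour sentence, state that if the chair does not do the review, the nominee must be the other independent member, the counselling psychologist.
2. In the terms of reference, state that the site PI and the clinical supervisor present events and answer questions but take no part in determining relatedness to PM+.

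With both changes, both decisions rest with the two members whom the protocol already describes as independent, so the label fits them. Dropping the word independent would remove the contradiction but leave the self-review gap open, so it is the weaker remedy.

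The cost is protocol wording only, with no new members, data or change in sample size. The one small burden is that either the chair or the psychologist must be reachable within 48 hours of an SAE report.
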